### Outcome measures

#### Primary outcome measure

The primary outcome measure will be the worst pain score experienced during HSG (by VAS). It will be collected by asking patients to rate “Your WORST pain intensity during HSG?”, ranging from no pain at all to worst pain possible.

#### Secondary outcome measures

Secondary outcome measures include: 1) pain score of the cognitive component (by VAS), collected by asking patients to rate “How much time did you spend thinking about your pain during HSG?”, ranging from none of the time to all of the time; 2) pain score of the affective component (by VAS), collected by asking patients to rate “How UNPLEASANT was your pain during HSG?”, ranging from not unpleasant at all to excruciatingly unpleasant; 3) worst pain score within 15 min after HSG (by VAS); 4) anxiety score before/during HSG (by GRS), collected by asking patients to rate “How much ANXIETY did you have before/during HSG?”, ranging from none at all to extremely anxious; 5) patient satisfaction score with pain management (by GRS), collected by answering the question: “How satisfied were you with the holistic pain management during HSG?”, ranging from not satisfied at all to completely satisfied; 6) patient acceptance score of pain management (by GRS), collected by answering the question: “How receptive were you to overall pain management during HSG?”, ranging from not receptive at all to completely receptive; 7) immersion perception score of the VR system (by GRS), collected by answering the question: “To what extent did you feel like that you went into the virtual reality environment while experiencing VR?”, ranging from “I did not feel like I went into the virtual reality environment at all” to “I went completely into the virtual reality environment” (for the VR group only); 8) physiological parameters; 9) adverse effects; and 10) HSG results.

### Data monitoring

A Data Monitoring Committee, which is independent of any competing interests, will be established immediately after the project launch. Members consist of one pain management specialist, one chief radiologist, two gynecology assistants working in the Radiology Department, and a senior academic statistician who will serve as the committee’s chair. Regular Data Monitoring Committee meetings will be held to discuss project issues, modify the protocol and monitor the progress of the study. No audit or interim analyses are planned.

### Data storage

Collected paper-based materials will be stored in locked filing cabinets in a locked office in Ningxia Medical University. All data will be collected in password-protected digital files on a password-protected computer in a locked office. Data entry will be performed continually throughout the study using the double-entry method. When the investigator inputs the information into the computer, each participant will be given a unique numeric code (ID number). As a result, the data acquired from patients are individually identifiable by the research team members only. Only deidentified information will be presented or published. To guarantee data quality, an independent clinical research assistant will verify the completeness and accuracy of the data by review of medical records once a month. Authorship will follow guidelines recommended by the International Committee of Medical Journal Editors (ICMJE).

### Sample size determination

The worst pain severity as the primary end-point measure is employed to estimate sample size in the current research according to previous studies on physical therapy for pediatric burn injury pain and dentalgia pain [19, 24]. According to our previous study on breakthrough pain [26], we used a pilot trial to determine the sample size. Fourteen subjects recruited in May 2019 were invited to the pilot trial. Seven of them were included in the VR intervention group during HSG, and worst pain scores of two parallel groups were recorded at T1. The sample size calculation formula is based on a two-group, parallel controlled design:
$$ \mathrm{n}=\frac{\left({{\mathrm{q}}_1}^{-1}+{q_2}^{-1}\right){\left({t}_{\alpha /2}+{t}_{\beta}\right)}^2{\sigma_c}^2}{\delta^2} $$where *n* represents the total sample size of the whole study, *σ*_c_ represents the standard deviation, *δ* represents the between-group difference with clinical significance, and q1 and q2 are the sample size ratio of the two groups (q1 = q2 = 0.5). According to the preliminary test, the worst pain score experienced during HSG reported by all blank control group participants (*n* = 7) revealed a mean (standard deviation (SD)) of 6.50 (2.26) out of 10. Participants (*n* = 7) in VR group reported a mean (SD) of 5.61 (0.93). The standard deviation of the whole sample (*n* = 14) was 1.72. At an *α* value of 0.05, a power of 90% (β = 0.10), and given a two-tailed test, we obtained *σ*_c_ = 1.72, *δ* =  ∣ *μ*_1_ − *μ*_2_∣ = 0.89. These data were used to calculate the value of the overall parameter to enter into the formula, and an *n* value of 157.02 was obtained. Thus, the rounded total sample size of the two groups was 158 (79 participants in each group). Allowing for a 20% dropout rate and withdrawals before study completion, we decided to enroll a total of 190 participants (95 participants in each group).

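### The 20% dropout allowance was added to 158 (giving 190) instead of dividing 158 by 0.8 (giving 198); this minor arithmetic slip costs about one point of power if 190 is the target and nothing if the abstract's 200 is

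*Protocol article*

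**What the plan says.** All the sample size figures are in the protocol article, section Sample size determination. The design values are introduced with "At an *α* value of 0.05, a power of 90% (β = 0.10), and given a two-tailed test". The spread comes from the pilot: "The standard deviation of the whole sample (*n* = 14) was 1.72". The control group "revealed a mean (standard deviation (SD)) of 6.50 (2.26) out of 10", and the women "in VR group reported a mean (SD) of 5.61 (0.93"), so the difference to detect is 0.89. Allocation is equal: "q1 and q2 are the sample size ratio of the two groups (q1 = q2 = 0.5"). From these inputs "an *n* value of 157.02 was obtained", and "the rounded total sample size of the two groups was 158 (79 participants in each group").

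The next sentence moves from the number needed to the number enrolled: "Allowing for a 20% dropout rate and withdrawals before study completion, we decided to enroll a total of 190 participants", which is 95 per group. The calculation behind that move is not shown.

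Two other places bear on the point. The abstract (Methods/design) gives an enrolment target of 200, with no derivation. The section Statistical analysis names a t test for the primary outcome and says that every randomized woman is to be analyzed, with multiple imputation for missing values.

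**The concern.** The sample size paragraph links four figures: 90% power, 158 women needed, 20% dropout and 190 enrolled. If 158 are needed and 20% of those enrolled are lost, the enrolment figure is fixed by division, and 190 is not the result. It is what one gets by adding 20% of 158 to 158, which covers a smaller loss than the one named. The four figures therefore cannot all hold.

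What is at stake is modest. At its own assumed dropout, a trial stopped at 190 would end slightly below its own stated requirement. A reader who relies on the 20% allowance would also think the margin larger than it is. Because the abstract names another total, the document leaves open which figure closes recruitment.

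**Working it through.** **Inputs** (Sample size determination): two-sided alpha 0.05; power 90%; SD 1.72; difference 6.50 - 5.61 = 0.89; q1 = q2 = 0.5; dropout 20%; enrolment 190. From the abstract: enrolment 200.

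**Step 1. Reproduce the stated requirement.** The protocol's formula is n = (1/q1 + 1/q2) x (z for alpha/2 + z for beta)^2 x SD^2 / difference^2. With z values 1.96 and 1.282:

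4 x (1.96 + 1.282)^2 x 1.72^2 / 0.89^2 = 4 x 10.5106 x 2.9584 / 0.7921 = 157.02.

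This matches the stated figure (unrounded z values give 156.98). Rounded up to an even number it is 158, or 79 per group, so this step is sound.

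**Step 2. Reproduce the enrolment figure.**

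- Adding 20%: 158 x 1.2 = 189.6, so 190. This is the protocol's number.
- Allowing for a 20% loss among those enrolled: 158 / (1 - 0.20) = 197.5, so 198 (99 per group).

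The shortfall in enrolment is 198 - 190 = 8 women.

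**Step 3. What 190 provides.**

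- Remaining after a 20% loss: 190 x 0.8 = 152, or 76 per group, which is 158 - 152 = 6 below the requirement.
- Largest loss that still leaves 158: (190 - 158) / 190 = 32 / 190 = 16.8%.

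**Step 4. Power at each size.** With m women per group, the standardized shift is 0.89 / (1.72 x sqrt(2/m)). The normal approximation compares it with 1.96. The noncentral t version, which matches the planned t test, uses 2m - 2 degrees of freedom.

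| Case | Women with an observed score | Power, normal | Power, noncentral t |
|---|---|---|---|
| 190 enrolled, 20% lost | 152 (76 per group) | 89.1% | 88.7% |
| Stated requirement | 158 (79 per group) | 90.2% | 89.8% |
| 198 enrolled, 20% lost | 158.4 (79.2 per group) | 90.3% | 89.9% |
| 200 enrolled, 20% lost | 160 (80 per group) | 90.5% | 90.2% |

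Example for 76 per group: 0.89 / (1.72 x sqrt(2/76)) = 3.19; 3.19 - 1.96 = 1.23; the normal probability below 1.23 is 89.1%.

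The cost of the dropout step alone is the first row against the second: 90.2 - 89.1 = 1.1 points (normal), or 89.8 - 88.7 = 1.1 points (noncentral t).

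**The case against.** A reader might infer that the trial fails to deliver its stated 90% power. The document does not support that, for several reasons.

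- **The enrolment target is not settled.** The abstract gives 200, and 200 x 0.8 = 160 meets the requirement with 90.2% to 90.5% power. The 190 is the only derived target, but nothing says that it overrides the 200. Whether 90% is missed depends on which figure governs.
- **The loss is about one point.** Part of the distance between 88.7% and 90% comes from using the t distribution. On that basis even the full 158 gives 89.8%, and the corrected 198 gives 89.9% after a 20% loss. Only about 1.1 points belong to the dropout step.
- **A 20% loss may not occur.** Up to 16.8%, 190 is enough. Allocation is revealed after baseline data taken just before the procedure, the procedure lasts about 20 minutes, and the primary score is recorded immediately afterwards. Heavy loss of that score looks unlikely, although this is inference: the document reports no observed dropout rate.
- **The inputs are far less certain than the correction.** The SD comes from 14 women. Assuming normality and 12 degrees of freedom, a rough 95% interval is 1.23 to 2.84. Since n scales with SD squared, the required total runs from about 81 to 428 at the same difference. Eight women are small beside that.

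All of this stands and limits the importance of the point. None of it makes 190 the right number for a 20% dropout rate.

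Multiple imputation is a weaker defense. It keeps every randomized woman in the analysis, but it does not restore the information in an unobserved score. The primary outcome is a single post-procedure rating, and women must be free of pain beforehand, so no informative baseline value of it exists. I assume that little would be recovered; the article does not list the imputation variables. The plan itself treats dropout as a loss by inflating for it.

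**Conclusion.** The arithmetic is wrong as written. The requirement of 158 reproduces, but the step to 190 adds 20% where it should divide by 0.8; the correct figure is 198 (99 per group).

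The consequence is small and conditional. If 190 governs and 20% are lost, 152 women remain, 6 fewer than stated, and power is about 89%, roughly one point below plan. If 200 governs, 160 remain and 90% is met. The point is a minor correction and gives no ground for doubting the trial's ability to answer its primary question.

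These figures rest on the protocol's own difference of 0.89 and SD of 1.72, on equal loss in both groups, and on counting women without an observed score as contributing nothing.

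**What to change.** Correct the dropout sentence in Sample size determination in one of two ways:

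- keep 190 and state that it allows for 16.8% dropout, or that it gives about 89% power at 20% dropout; or
- keep the 20% allowance and state 198 (99 per group) or the abstract's 200 (100 per group) as the target.

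In either case, make the abstract and Sample size determination give the same enrolment figure, so that the point at which recruitment closes is not open to choice.

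The first option costs one reworded sentence and no extra women, plus a matching change in the abstract. The second means 8 or 10 more women than 190. That appears feasible: the article reports about 1000 procedures a year at the site, and 22 women recruited when it was submitted. The formula, the requirement of 158 and the analysis need no change for this point.

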### Statistical analysis

In this study, all data will be collected by a specialized researcher. A blinded statistician who is not involved in this trial will perform statistical analysis using SPSS version 22.0 (Chicago, IL, USA). A complete statistical analysis plan will be generated in advance by the trial statistician. All randomized participants should be included in the analysis, and missing data will be handled using multiple imputation. Data will be analyzed initially on an intention-to-treat basis. For comparing the primary outcome between the two parallel groups, additional per-protocol analysis will be performed, and reasons for any protocol violations will be reported. We will consider all *P* values <0.05 to be statistically significant.

Descriptive statistics will be used to describe the demographic features by means (SD), medians (interquartile ranges; minimum to maximum), and proportions (exact binomial 95% confidence intervals). A *t* test will be applied to determine the differences between the primary outcome. Secondary outcomes such as the amount of time spent thinking about pain, pain unpleasantness, worst pain within 15 min after HSG, anxiety, satisfaction, and acceptance with pain management will use *t* tests or Mann–Whitney tests. Chi-squared tests or Fisher’s exact test will be used for HSG results and adverse reactions. When comparing the physiological parameters, the repeated measures analysis of variance will be used. Pearson correlation analysis will be used to analyze the relationship between immersion perception score of the VR system and the three pain dimensions.

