### Study participants

Women will be recruited into the study according to the following inclusion criteria: 1) indications for HSG including infertility, recurrent miscarriage, and other miscellaneous reasons [5]; 2) aged 20–45 years; 3) willing to participate in the study and sign informed consent; and 4) no signs of pain before HSG.

The exclusion criteria are: 1) use of antidepressants or sedatives; 2) presence of psychiatric disorders; 3) recent receipt of analgesics within 6 h; 4) allergy to contrast medium or iodine; 5) a recent history of acute pelvic inflammatory disease; 6) visual acuity <1.0 or hearing abnormity; 7) susceptible to motion sickness; 8) operator difficulty due to cervical adhesion or congenital variation, or completing the examination after multiple operations.

In the Radiology Department, the HSG procedure will be carried out on each weekday by two gynecology assistants (both female who have worked in the HSG room for >10 years). The results of the HSG will be analyzed by a Chief Radiologist (who has worked in the HSG room for >10 years). These two gynecology assistants will receive training from the protocol conceiver.

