Any observed adverse effects will be carefully evaluated and recorded by the investigators. The expected adverse effects include gastrointestinal adverse reactions (nausea, vomiting), adverse effects on the cardiovascular system (arterial hypotension and bradycardia) and any other discomfort (pallor, sudation, palpitation, dizziness, syncope). If any adverse effects take place, health care givers will administer corresponding treatment or nursing care. All severe adverse reactions and solutions during the procedure will also be noted. HSG results (both tubes patent, one or both fallopian tubes occluded and/or impaired patency) should be recorded and compared. The physiological indexes will be monitored in terms of treatment safety with an electronic manometer (OMRON, HEM-7120) and oximeter (PC-60B).

Participants’ demographic data, relevant medical history and baseline anxiety level, as well as pulse rate, digital monitoring of oxygen saturation and noninvasive monitoring of blood pressure, will be collected at baseline (T0) before the procedure. Patients will complete a series of assessment including three pain dimensions, physiological parameters (including pulse, blood pressure and oxygen saturation), anxiety level during HSG, satisfaction and acceptance of pain management and adverse reactions along with the immersion perception of the VR system (for the VR group only) immediately after the procedure (T1). HSG results and worst pain will be recorded 15 min (T2) after the procedure. To promote participant retention, every woman who completes all data collections will receive a free overall analysis of the HSG results by an experienced gynecologist.

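### Baseline anxiety is recorded before allocation is revealed, but the planned tests of anxiety and worst pain do not use it; the tests are valid but forgo precision

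*Protocol article*

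**What the plan says.** Protocol article, Statistical analysis: the primary outcome, worst pain on a 0–10 VAS, is compared by a t "test will be applied to determine the differences between the primary outcome". The secondary scores follow in one list: "worst pain within 15 min after HSG, anxiety, satisfaction, and acceptance with pain management will use" t tests or Mann–Whitney tests. No covariate is named for either analysis, and the text does not say whether the t test is the pooled or the unequal-variance form. A full statistical analysis plan is promised there.

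Protocol article, Measurements: the T0 data include "relevant medical history and baseline anxiety level". Under Randomization, allocation concealment and blinding, the allocation is revealed only after baseline data have been collected.

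Protocol article, Secondary outcome measures: the fourth outcome is given as "anxiety score before/during HSG (by GRS"), so the pre-procedure and during-procedure ratings sit under one outcome label and use the same question.

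Protocol article, Study participants: women must have "no signs of pain before HSG", so there is no baseline pain score to adjust for.

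Protocol article, Sample size determination: the calculation is for an unadjusted two-group comparison. In the pilot, control women "revealed a mean (standard deviation (SD)) of 6.50 (2.26) out of 10", and the VR group had 5.61 (0.93), with seven women in each group.

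**The concern.** Anxiety during HSG is the first-named secondary objective. A woman's rating before the procedure is likely to predict her rating during it. If the arms differ by chance at T0, part of that difference carries into the unadjusted comparison, and neither planned test removes it. Because the T0 rating precedes disclosure of allocation, treatment cannot have changed it. It is therefore a proper covariate, and it carries no information about the effect of VR when listed as an outcome.

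For worst pain, the Measurements section itself says that emotion helps regulate how pain is perceived, so baseline anxiety is a plausible prognostic variable. Ignoring it may cost some power on the primary outcome. The evaluable target leaves little spare power if the full 20% dropout allowance is used.

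A side question is whether the very different pilot SDs, together with a simple randomization that can give unequal arms, disturb the t test.

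**Working it through.** **1. Reproducing the plan's own figure.** Inputs from Sample size determination: difference 0.89, SD 1.72, q1 = q2 = 0.5, two-sided alpha 0.05, power 90%.

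n = (1/0.5 + 1/0.5) × (1.96 + 1.282)² × 1.72² / 0.89² = 157.02.

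This matches the stated total, rounded to 158 (79 per arm). The formula has no covariate, so it agrees with the unadjusted t test.

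**2. Power when the dropout allowance is used in full.** Enrolment in that section is 190, and 190 × 0.8 = 152, or 76 per arm. The standard error is 1.72 × √(2/76) = 0.279 and 0.89/0.279 = 3.19. On the noncentral t distribution with 150 degrees of freedom, power is 88.7% (89.1% by the normal approximation).

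**3. Gain for worst pain from adjusting for baseline anxiety.** Adjustment replaces the SD by 1.72 × √(1 − r²), where r is the correlation of baseline anxiety with worst pain. The article gives no value for r, so a range is assumed. The equivalent gain in patients is 1/(1 − r²) − 1.

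| Assumed r | Residual SD | Equivalent extra patients | Power at 76 per arm |
|---|---|---|---|
| 0 | 1.72 | 0% | 88.7% |
| 0.2 | 1.69 | 4% | 89.9% |
| 0.3 | 1.64 | 10% | 91.3% |
| 0.4 | 1.58 | 19% | 93.3% |

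**4. Gain for anxiety during HSG.** The same formula applies, with r now the correlation between two ratings on the same item. It is also not given. At an assumed 0.5 the variance falls by 0.5² = 25%, and at 0.6 by 36%. The same adjustment removes the part of any chance T0 difference that predicts the later score.

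**5. Unequal variances.** The pilot SD ratio is 2.26/0.93 = 2.43 (variance ratio 5.9). With seven women per group, its 95% confidence interval is 1.01 to 5.86. Taking the pilot SDs as true, simulation with normal data gives these type I error rates:

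| Control / VR | Pooled t | Welch t |
|---|---|---|
| 79 / 79 | 5.1% | 5.0% |
| 95 / 95 | 5.2% | 5.1% |
| 100 / 100 | 5.0% | 5.0% |
| 88 / 102 | 6.4% | 5.0% |
| 102 / 88 | 4.0% | 5.0% |
| 81 / 109 | 7.8% | 5.0% |
| 109 / 81 | 3.0% | 5.0% |

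Under simple randomization of 190 women, the size of one arm lies between 82 and 108 with 95% probability, so 81/109 is just outside that range. Averaged over all splits, the pooled test's error is 5.2%. Welch costs almost nothing: at 79 per arm its power is 89.4%, against 89.6% for the pooled test.

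**The case against.** The strongest reply is that nothing stated here is wrong. An unadjusted t test is valid after randomization, agrees with the sample size formula, and has about 90% power at the evaluable target of 79 per arm. Covariates and the form of the t test could be set in the promised analysis plan, which is not shown. The gain for pain rests on an assumed correlation, and at 0.2 it is only 1.2 percentage points of power. Baseline anxiety is also a different construct from pain. All of this stands, and it limits the point to an improvement in efficiency.

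It does not dispose of the point, because the article does name the tests, and both alternatives for anxiety ignore that outcome's own baseline.

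Three stronger readings are tempting and are not supported:

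- A reader might infer from the pilot SDs that the primary P value will have the wrong error rate. At the planned 1:1 sizes it does not. The distortion needs a clearly unequal split and the pooled form, which the article does not specify, and the SD ratio rests on seven women per group.
- A reader might infer that baseline anxiety will be tested between arms. The outcome label allows that reading, but Statistical analysis says only anxiety.
- A reader might want to adjust for the operator as well, since two gynecology assistants perform the procedure. Operator is not among the variables listed under Measurements.

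**Conclusion.** The point holds as a missed efficiency gain, not as an error in the primary test. It is firmest for anxiety during HSG, where a baseline on the same item is recorded and left unused; at assumed correlations of 0.5 to 0.6, adjustment would cut the variance by 25% to 36%. For worst pain the benefit is smaller and conditional: at correlations of 0.2 to 0.4 and 76 women per arm, power rises by 1.2 to 4.6 percentage points (88.7% to 89.9–93.3%). These figures assume the protocol's difference of 0.89 and SD of 1.72, and a roughly linear relation between baseline anxiety and the outcome. No material error-rate fault is claimed.

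**What to change.** Before unblinded data are analysed, state in the analysis plan:

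1. Anxiety during HSG is analysed by ANCOVA with arm and baseline anxiety. The pre-procedure score is a covariate and a baseline descriptor, and is removed from the outcome label.
2. The primary analysis is a linear model of worst pain on arm and baseline anxiety, reporting the adjusted mean difference with its 95% confidence interval. The unadjusted t test is kept as a supportive result.
3. The linear models use heteroscedasticity-robust standard errors and the unadjusted test is the Welch form. This is a safeguard against unequal arms with unequal SDs, and it removes a choice between two P values after the data are seen.

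The cost is wording only. Baseline anxiety is already in the T0 data set, and no visit, question or patient is added. The sample size need not change, since the unadjusted calculation is the conservative one if baseline anxiety is prognostic.

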### Randomization, allocation concealment and blinding

A simple random sampling method will be used in our study. Patients who are scheduled for HSG and meet the eligibility criteria will be randomly allocated into either the blank control group or the VR group at a 1:1 ratio. The randomization sequences will be generated in advance with a computerized random number generator (random.org). This is performed by a statistical expert who is not involved in this trial. A sealed opaque envelope will be used to store the randomization sequences of all allocations. The random number table will be kept confidential by the full-time secretary of this project. Baseline data will be recorded as close to immediately before the HSG procedure as possible. After baseline data collection, the allocation will be revealed. Blinding is not feasible.

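### Anxiety and the physiological parameters have a pre-allocation baseline, but the planned tests do not adjust for it, which costs precision on secondary outcomes

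*Protocol article*

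**What the plan says.** **Timing of the baseline.** The section on randomization, allocation concealment and blinding states "Baseline data will be recorded as close to immediately before the HSG procedure as possible", and then "After baseline data collection, the allocation will be revealed". The T0 values therefore cannot carry a treatment effect.

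**What is measured when.** The Measurements section places the first anxiety score, pulse, oxygen saturation and blood pressure at T0; the sentence that lists them ends "noninvasive monitoring of blood pressure, will be collected at baseline (T0) before the procedure". For T1, directly after HSG, it names "physiological parameters (including pulse, blood pressure and oxygen saturation), anxiety level during HSG, satisfaction and acceptance of pain management", among other items. At T2, 15 minutes later, it lists only the HSG results and worst pain.

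**How these outcomes are analysed.** Statistical analysis assigns anxiety to two-sample tests, t or Mann–Whitney, in the clause "worst pain within 15 min after HSG, anxiety, satisfaction, and acceptance with pain management will use". For pulse, blood pressure and oxygen saturation, "When comparing the physiological parameters, the repeated measures analysis of variance will be used". No baseline covariate is named for any outcome, and the ANOVA term that tests treatment is not identified.

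**How the anxiety outcome is defined.** Secondary outcome measures lists "anxiety score before/during HSG (by GRS"), which places the pre-allocation score inside the outcome definition.

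**The concern.** A baseline taken before allocation is most useful as a covariate, because it explains part of the T1 variation without being affected by treatment. The article instead sets it aside (anxiety) or lets it enter as one of the repeated outcomes (physiological parameters).

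Anxiety during HSG and safety, the latter partly through the physiological indexes, are among the secondary objectives in Study design, alongside acceptance and satisfaction. For the safety measures in particular, an imprecise comparison leans towards showing no difference and could be read as reassurance.

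Allocation is by simple randomization with no balancing, so a chance difference D between arms at T0 is possible. With equal variances at T0 and T1, and correlation rho between them, such a difference shifts the T1-only estimate by rho × D and the change-score estimate by −(1 − rho) × D. ANCOVA removes both shifts.

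**Working it through.** **The plan's own figure first.** Sample size determination gives n = 4(z₀.₉₇₅ + z₀.₉₀)² × 1.72² / 0.89². With z rounded to 1.96 and 1.282 this is 157.02, as stated; with unrounded z it is 156.98. Both round up to 158, or 79 per arm. This calculation is for worst pain. The article gives no power for anxiety or the physiological parameters, so 79 per arm is used below only as the evaluable number.

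**Assumptions.** The documents give neither the T0–T1 correlation rho nor an effect size for these outcomes. I take rho = 0.3, 0.5 and 0.7, a T1 effect of d = 0.4 SD, equal SD (set to 1) at T0 and T1, equal T0 means in expectation, a two-sided 5% level, and normal approximations.

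**Estimators with T0 and T1 only, n per arm.**
- T1-only t test: estimates d, variance 2/n.
- ANCOVA on T0: estimates d, variance (2/n)(1 − rho²).
- ANOVA group-by-time term, which with two time points is the change-score t test: estimates d, variance (2/n) × 2(1 − rho).
- ANOVA group main effect: compares the mean of T0 and T1, so it estimates d/2, variance (2/n)(1 + rho)/2.

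**Variance of ANCOVA relative to the others.**
- Against T1-only: 1 − rho² = 0.91, 0.75, 0.51, so 9%, 25% and 49% smaller.
- Against the change score: (1 − rho²) / [2(1 − rho)] = (1 + rho)/2 = 0.65, 0.75, 0.85, so 35%, 25% and 15% smaller.

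**Power at n = 79, d = 0.4.** The base standard error is √(2/79) = 0.159. At rho = 0.5:
- T1-only: 0.4/0.159 = 2.51, power 71%.
- ANCOVA: standard error 0.159 × √0.75 = 0.138; 0.4/0.138 = 2.90, power 83%.
- Group-by-time: standard error 0.159 × √1 = 0.159, power 71%.
- Group main effect: standard error 0.159 × √0.75 = 0.138; 0.2/0.138 = 1.45, power 31%.

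Over the range:

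| Analysis | rho 0.3 | rho 0.5 | rho 0.7 |
|---|---|---|---|
| ANCOVA | 75% | 83% | 94% |
| T1-only t test | 71% | 71% | 71% |
| Group-by-time | 57% | 71% | 90% |
| Group main effect | 34% | 31% | 28% |

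**Simulation check.** A separate run used 4,000 replicates at each rho and an effect of 0.446 SD, which gives the T1-only test 80% power. Its results agreed with the formulas to within about two percentage points. The main-effect estimate came out at 0.50 of the true T1 effect.

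**If T2 were also measured.** With the same effect at T1 and T2, the main effect averages 0, d and d, giving 2d/3. The dilution is then one third instead of one half.

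**The case against.** The strongest reply is that nothing here is invalid. Under randomization the T1-only test and the group-by-time test are unbiased and keep their type I error. Only secondary outcomes are involved, and the gain depends on a correlation the documents do not give. At rho = 0.3 ANCOVA gains about four points of power over the T1-only test; at rho = 0.7 it gains about four over group-by-time. The article also promises a complete analysis plan, which could name the ANOVA term. All of that stands. It does not remove the point, because the article already names the tests, and even their favourable readings are less precise than ANCOVA at every rho in the range.

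A reader might infer three stronger things that the documents do not support.

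- *That the repeated measures ANOVA dilutes the effect.* This follows only if the group main effect is the treatment test. The article does not say so, and group-by-time is the natural choice when T0 precedes allocation. The halving also needs exactly two time points. Measurements supports two, but the abstract speaks generally of monitoring at 15 minutes as well, and the schedule figure is not visible in the text at hand.
- *That baseline anxiety will be tested as an effect of treatment.* The outcome wording covers the score before the procedure, but Measurements calls it a baseline level, the abstract and Study design name only anxiety during HSG, and Statistical analysis says just anxiety. This is loose wording, not a stated test.
- *That the main result is affected.* Worst pain during HSG has no T0 score, and absence of pain beforehand is an inclusion criterion.

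One practical objection also holds: the GRS is bounded at 0 to 10 and may be skewed, so dropping the Mann–Whitney option should leave something in its place.

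**Conclusion.** The point holds as a loss of efficiency on secondary outcomes, together with an unnamed treatment term in the ANOVA. It is not a bias in the T1-only or group-by-time comparison. Its size depends on which planned test is meant. The T1-only test loses most when rho is high, and the change-score test loses most when rho is low. Dilution by half, or by a third with T2, is conditional on the main effect being used. All power figures rest on the assumed 0.4 SD effect, the assumed range of rho, equal variances, and 79 evaluable women per arm. The change is worth making because it improves precision at almost no cost; the trial's primary conclusion does not depend on it.

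**What to change.** - Analyse T1 anxiety and each T1 physiological parameter by ANCOVA, with arm and that variable's own T0 value in the model. Report the adjusted mean difference with its 95% confidence interval.
- If the physiological parameters are in fact also taken at T2, use a repeated measures model with T1 and T2 as outcomes and T0 as covariate, and state which contrast tests treatment.
- Keep a rank-based or robust sensitivity analysis for skewed 0–10 GRS scores.
- In Secondary outcome measures, limit the anxiety outcome to the score during HSG and use the score before it only as the covariate.

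The cost is a change of wording in the analysis and outcome sections. Every value needed at T0 and T1 is already scheduled, and neither the sample size nor the primary analysis changes.
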